### Participant timeline

Both wheezing participants and healthy participants follow the same timeline (Fig. 1). Participants enrol in the study, after informed consent, at the age of 2 or 3 years old. At the baseline visit, the wheezing children that participate in the RCT will be randomised into either the intervention group or the usual care group. All children included in the study will perform the study-related procedures, including the breath test, at the baseline visit (see section “data collection” and Fig. 2). The children that will be allocated to the intervention arm of the RCT will receive their probability diagnosis and corresponding treatment advice within three months of the baseline visit. All children will be invited for the annual, study-related hospital visits until the age of 6. The performed study procedures at each visit are illustrated in Fig. 2. All parents will receive online questionnaires prior to the annual visit (a list of the questionnaires is provided in Fig. 3). Parents of children that participate in the RCT will also receive questionnaires on disease control and healthcare related expenditures with a 3-month interval. At the age of 6, a final diagnosis will be made based on respiratory symptoms, use of medication, and objective lung function measurements as reported previously [22].

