### Questionnaires

Parents will be asked to complete several questionnaires during the study to assess asthma control, quality of life, and utilisation of health care and societal resources [40–42]. The questionnaires will be provided as e-version and will be sent to the parents two weeks before the annual clinical visits. Two questionnaires will be sent at a three-monthly interval: the questionnaires on asthma control (TRACK) and on utilisation of health care and societal resources.

*TRACK* Parents will be asked to complete the TRACK questionnaire at a 3-month interval. The TRACK questionnaire is a validated questionnaire on asthma control specifically developed for use in this age group, independent of the diagnosis. A score of 80 or more is defined as well controlled disease. The TRACK score is sensitive and reliable, and an increase of 10 points was found to be the ‘minimally important difference’ [43].

*ISAAC questionnaire (Core Questionnaire and Environmental Questionnaire)* The Core Questionnaire and the Environmental Questionnaire have been developed by the ISAAC steering Committee [44]. This questionnaire is used in this study to assess asthma, allergic rhinoconjunctivitis and eczema in all participants and to assess a variety of environmental factors.

*EQ-5D-Y (proxy version)* The EQ-5D-Y questionnaire is a validated child-friendly version of the EQ-5D on quality of life that comprises the following five dimensions with three answer levels (“no problems,” “some problems,” and “a lot of problems”): mobility, looking after myself, doing usual activities, having pain or discomfort and feeling worried, sad or unhappy. It also includes a visual analogue scale (VAS), which gives an overall assessment of the child’s health status in a scale from 0 (worst imaginable health state) to 100 (best imaginable health state). In the proxy version, the caregiver is asked to rate the child’s health-related quality of life (HRQoL). The EQ-5D-Y proxy-version has been tested in children as from 4 years of age [45], which revealed that some domains (e.g. self-care) were sometimes perceived by the parents as not suitable to young children. However, no alternative preference-based measure is currently available or has a validated proxy-version for use in preschool children.

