### Assessment of improvement in health gain and costs of care with the application of the breath test in wheezing preschool children

The effect of the intervention will be assessed by comparing the outcome measures between the intervention and the usual care group in the RCT. Dichotomous parameters will be tested with the chi-square test. Continuous variables will be tested for significance with the unpaired t-test for normally distributed parameters and the Mann Whitney-U test in case of a not-normal distribution.

Total treatment costs will be calculated by multiplying resource use with the costs per unit. Resource use (visits to the general practitioner or specialist, emergency visits, hospital admission, lung function tests and other diagnostic procedures, the breath test, (over-the-counter) medication, and lost work days by parents due to sickness of the child) will be obtained from a specially designed questionnaire with a recall period of three months. The parents will fill out this questionnaire at baseline and at 3 months interval during the follow-up. Sources for valuation of the costs will be cost-prices of the Dutch manual for costing and cost-prices from the Dutch pharmacotherapeutic compass [45, 47–49] (reference data 2022). If necessary, local hospital cost-prices will be used, which are largely based on integral cost-prices from the Dutch hospitals [50]. Absence of work reported by the parents will be calculated by using the friction cost method, which is recommended by the Dutch manual for costing [47, 48].

The cost-effectiveness analysis from the healthcare perspective will be based on symptom control according to the TRACK questionnaire at 1 year follow-up (primary outcome measure). The cost-effectiveness analysis from the societal perspective will be based on the EQ-5D-Y. The EQ-5D-Y will be completed at baseline and at 3 months intervals during the follow-up, and will be filled out by one of the parents.

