A cost-effectiveness analysis will be performed from a societal and healthcare perspective with a time horizon of 2 years. Incremental cost-effectiveness ratios will be calculated as societal cost per QALY (societal perspective) and health care cost per additional child with control of asthma-like symptoms (healthcare perspective). Standard sensitivity- and bootstrap analysis will be performed to address uncertainty regarding costs and cost-effectiveness outcomes. Cost-effectiveness acceptability curves will be constructed reflecting the probability that the diagnostic breath test is cost-effective for a range of threshold values. Costs and effects after one year will be discounted at 4.0% and 1.5% respectively, according to the Dutch guidelines for health economic evaluation [45, 48].

All outcome parameters and corresponding outcome measures and methods of analysis are listed in Table 2. The large number of patients (*n* = 220) allows better representation of specific subgroups of specific age, background (primary or secondary/tertiary care), genetic predisposition, and geographic area. All these parameters will be measured and included in the multivariable analysis in order to assess possible influences on outcome. Intention-to-treat analyses will be applied. We will execute two subgroup analyses: one for age and one for level of care (first-line versus secondary/tertiary care). Two-sided *p*-values < 0.05 (with correction for multiple testing) will be regarded as statistical significant.

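### The healthcare-perspective ICER pairs 2-year costs with 1-year control, the EQ-5D-Y schedule is stated in two conflicting ways, and skewed costs would be compared by a rank test rather than by means

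*Protocol article*

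**What the plan says.** All places are in the protocol article.

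**Effect and horizon.** The statistical section on health gain and costs of care states that the healthcare-perspective analysis "will be based on symptom control according to the TRACK questionnaire at 1 year follow-up (primary outcome measure"). It then says: "A cost-effectiveness analysis will be performed from a societal and healthcare perspective with a time horizon of 2 years". The healthcare ratio is defined as "health care cost per additional child with control of asthma-like symptoms (healthcare perspective"), with no time point attached. On discounting: "Costs and effects after one year will be discounted at 4.0% and 1.5% respectively". Under Outcomes, the primary outcome is TRACK control at both 1 and 2 years. The primary row of Table 2 lists 1 year only.

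**Utilities.** The same section says: "The EQ-5D-Y will be completed at baseline and at 3 months intervals during the follow-up". The Questionnaires section sends questionnaires before the annual visits and then singles out two for more frequent use: "Two questionnaires will be sent at a three-monthly interval: the questionnaires on asthma control (TRACK) and on utilisation of health care and societal resources". Participant timeline agrees that parents in the RCT "will also receive questionnaires on disease control and healthcare related expenditures with a 3-month interval". The section Cost-effectiveness takes the QALY from the EQ-5D-Y.

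**Cost comparison.** Continuous variables are tested "with the unpaired t-test for normally distributed parameters and the Mann Whitney-U test in case of a not-normal distribution". Table 2 repeats this pair of tests in the rows for healthcare resource use and costs and for costs outside healthcare. The cost-effectiveness row has sensitivity and bootstrap analysis instead, and the text extends that bootstrap to uncertainty in costs as well as in cost-effectiveness.

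**The concern.** Reduction in costs stands next to health gain in the primary objective, so the economic analysis carries much of the trial's message.

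- A ratio whose numerator covers 2 years and whose denominator is a state at 1 year describes neither period. It also feeds the cost-effectiveness acceptability curve for the healthcare perspective.
- If the EQ-5D-Y goes out only with the annual questionnaires, short losses of utility around wheezing episodes cannot be recovered later.
- A budget or a saving depends on mean cost. A rank test answers whether one arm's costs tend to be higher than the other's, which can differ from the mean comparison when a few children generate very large costs.

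**Working it through.** The protocol states no cost, utility or ICER figure, so there is no economic number to reproduce. The figures below are illustrations on assumed inputs. The only inputs from the protocol are the discount rates (4.0% for costs, 1.5% for effects, after year 1), the planned difference in control (40% − 20% = 0.20, Sample size) and 110 children per arm.

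**1. Period mismatch**

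*Against a matched 1-year ratio.* Let the year-2 cost difference be f times that of year 1. The effect is the same in both ratios, so the planned ratio differs by the factor 1 + f/1.04:

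| f (assumed) | factor |
|---|---|
| 0 | 1.00 |
| 0.5 | 1.48 |
| 1 | 1.96 |
| 1.5 | 2.44 |

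*Against a matched 2-year ratio.* The costs are now identical and cancel. With an effect of 0.20 at 1 year and e2 at 2 years, the planned ratio divided by the matched one is (e2/1.015)/0.20:

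| e2 (assumed) | factor |
|---|---|
| 0.10 | 0.49 |
| 0.15 | 0.74 |
| 0.20 | 0.99 |
| 0.25 | 1.23 |
| 0.30 | 1.48 |

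If the effect fades by year 2, the plan makes the cost per controlled child look too small. If it grows, too large. If it is constant, only the 1.5% discount remains. Discounting effects after year 1 makes sense for QALYs, but there is nothing to discount in a control rate taken at 1 year.

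**2. EQ-5D-Y schedule**

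Over 2 years, 3-monthly completion gives utilities at 0, 3, …, 24 months (9 points). Completion at annual visits gives 0, 12 and 24 months (3 points). With the trapezium rule, a drop of d at a single intermediate 3-month point lowers the QALY total by d × 0.25:

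| d (assumed) | loss, 3-monthly data | loss, annual data |
|---|---|---|
| 0.1 | 0.025 | 0 |
| 0.2 | 0.05 | 0 |
| 0.3 | 0.075 | 0 |

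**3. Rank test on costs**

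Assume lognormal costs with log-SD 1.0 in one arm and 1.4 in the other, 110 per arm, 4000 simulated trials, two-sided 5% level:

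| scenario | Mann-Whitney rejects | Welch t-test rejects |
|---|---|---|
| equal medians, mean ratio exp((1.4² − 1.0²)/2) = exp(0.48) = 1.62 | 5% | 39% |
| equal means, different spread | 80% | 7% |

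The two can also point in opposite directions. If the more variable arm has a log-mean lower by 0.24, its median is exp(−0.24) = 0.79 times the other's, while its mean is exp(−0.24 + 0.48) = exp(0.24) = 1.27 times the other's.

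**The case against.** The case for the plan has four parts, and each has some force.

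*Scope.* Only the healthcare ratio is mismatched. The societal analysis uses QALYs over the stated horizon. This stands.

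*Size.* A reader might infer that the ICER is roughly doubled, from 1 + 1/1.04 = 1.96. The documents do not support that as the size of the error. It assumes an equal cost difference in both years, and no cost pattern is given. The breath test itself is a cost and the result is released within three months of baseline, so a constant difference is not obvious. Against a 2-year ratio, which fits the stated horizon, the factor cancels altogether. What remains is the range shown above.

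*EQ-5D-Y.* A reader might infer that QALYs will rest on three utilities. That is not established. The costing section schedules the 3-monthly EQ-5D-Y expressly, Data collection speaks only of a subset sent 3-monthly without naming it, and Fig. 3, the questionnaire schedule, was not visible in the text reviewed. It is a contradiction, not a proven gap in the data. Even if Fig. 3 lists the EQ-5D-Y 3-monthly, two text sections would still disagree with it. Annual data would also still yield a QALY, only a coarser one.

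*Rank test.* A reader might infer that it undermines the ICER. It does not enter the ICER, and the planned bootstrap covers costs too. It applies only if costs are non-normal, which is an assumption, though a usual one when some children are admitted to hospital. The part that survives is that Table 2 still assigns the between-arm cost comparison a test that does not address mean cost.

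**Conclusion.** The point holds in three limited parts, and none of them makes the economic evaluation as a whole unsound.

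1. The healthcare ICER is inconsistent as written: 2-year costs over 1-year control. Its size cannot be fixed from the protocol. It is 1.00 to 2.44 times a matched 1-year ratio if the year-2 cost difference is 0 to 1.5 times that of year 1. It is about 0.5 to 1.5 times a matched 2-year ratio if the effect moves from 0.20 to between 0.10 and 0.30.
2. The frequency of the EQ-5D-Y is contradicted between the costing section and two other sections. The consequence, loss of utilities between annual visits, follows only if sites act on the latter.
3. For skewed costs, the test named in Table 2 can miss a real difference in mean cost, find one where means are equal, or point the other way. The simulated rates depend on the assumed lognormal spreads.

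The changes are worth making because cost reduction is part of the primary objective and the remedies are cheap.

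**What to change.** - **Periods.** Make 2-year costs with TRACK control at 2 years the base case for the healthcare ICER, or use time in control from the 3-monthly TRACK. Add 1-year costs with 1-year control as a secondary analysis. State the time point in the definition of the ratio. No new data are needed, since control is already assessed at 1 and 2 years and every 3 months.
- **EQ-5D-Y.** Bring Participant timeline and Questionnaires into line with the 3-monthly completion that the QALY analysis states, and check Fig. 3 against them. If the questionnaire is already sent 3-monthly, this is wording only. If not, the cost is one short extra questionnaire per quarter for parents, and the intervals already missed should be reported.
- **Costs.** In the two cost rows of Table 2, replace the t-test/Mann-Whitney entry with the bootstrapped difference in mean costs and its 95% CI. The bootstrap is already planned, so this adds no work.

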### Sample size

*Randomised controlled trial* With a presumed percentage of well-controlled preschool children with asthma-like symptoms of 20% in the usual care group (based on reference [32, 33]), and of 40% in the intervention group, 91 patients in both groups are needed to detect this difference with an alpha of 0.05 and a power of 80%. Taking a dropout rate of 10% into account, we aim to include a total number of 220 preschool children with asthma-like symptoms.

*Prospective cohort study* For studies assessing the relationship between microbiome, transcriptomics, epigenetics, and atopic outcomes like asthma, a sample size of 70–80 is considered adequate [34, 35].

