**Randomised Controlled Trial**			
*Primary*			
Difference in the percentage of well controlled asthma-like symptoms after 1-year follow-up	I	TRACK-score	Unpaired t-test / Mann Whitney-U test
*Secondary*			
Pharmacotherapy	I, II, III, IV	Cumulative ICS dosage (fluticasone equivalent)	Mann Whitney-U test
Growth retardation	I, II, III, IV	SD deviation from target height	Unpaired t-test
Amount of exacerbations	I, II, III, IV	Amount	Chi-square test
Amount of hospital admissions	I, II, III, IV	Amount	Chi-square test
Quality of life child	I, II, III, IV	EQ-5-DY by proxy	Unpaired t-test / Mann Whitney-U test
Quality of life caretaker	I, II, III, IV	EQ-5-DY	Unpaired t-test / Mann Whitney-U test
Lung function (tremoflo)	I, II, III, IV	R_5_, R_5-20_, X_5_, X_5-20_, AX, F_res_ (baseline and % change after salbutamol)	Unpaired t-test / Mann Whitney-U test
Lung function (spirometry)	II, III, IV	FEV_1,_ FVC, MEF50 (baseline and % of change after salbutamol)	Unpaired t-test / Mann Whitney-U test
Absence of school and work (parents)	I, II, III, IV	Number of days	Chi-square test
Healthcare resource use and –costs	I, II, III, IV		Unpaired t-test / Mann Whitney-U test
Costs outside healthcare	I, II, III, IV	Euro	Unpaired t-test / Mann Whitney-U test
Cost-effectiveness	I, II, III, IV	Societal cost per QALY and health care cost per additional child with control of asthma-like symptoms	Sensitivity and bootstrap analysis

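### The listed analyses of EQ-5D-Y, costs and cost-effectiveness name no adjustment for baseline utility or baseline costs, although both are collected; this gives up precision that would cost almost nothing to recover

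*Protocol article*

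**What the plan says.** The section on health gain and costs of care sets out the economic evaluation. "Incremental cost-effectiveness ratios will be calculated as societal cost per QALY (societal perspective"), alongside health care cost per additional controlled child. The horizon is 2 years, effects after year 1 are discounted at 1.5%, and bootstrap, sensitivity analysis and acceptability curves are planned. The same section refers the reader to Table 2 for all methods of analysis. For cost-effectiveness Table 2 gives "Sensitivity and bootstrap analysis". For child quality of life and for costs it gives an unpaired t-test or Mann-Whitney test.

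Baseline data are available for both parts of the ratio. On utility: "The EQ-5D-Y will be completed at baseline and at 3 months intervals during the follow-up". On resource use: "The parents will fill out this questionnaire at baseline and at 3 months interval during the follow-up", with a 3-month recall period, so the baseline form describes the time before randomisation.

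The section also plans a multivariable analysis that names age, level of care, genetic predisposition and geographic area. It names neither baseline utility nor baseline cost, and it does not say which outcomes it covers. Under Allocation and blinding, randomisation is stratified by measurement centre alone.

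The schedule is inconsistent. Participant timeline and Questionnaires list only disease control (TRACK) and resource use or expenditure as 3-monthly. EQ-5D-Y is not among them.

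**The concern.** A child's baseline utility is usually correlated with the same child's later utilities, and if QALYs are computed as an area under the utility curve it also forms the first part of that area. When the arms differ at baseline by chance, the unadjusted QALY difference is expected to differ in the same direction. The same holds for costs to the extent that earlier costs predict later ones. A bootstrap of unadjusted arm means reports this variation as sampling error but does not reduce it. A regression with the baseline value as a covariate does.

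At stake are the width of the interval for incremental QALYs and costs, and the position of the acceptability curve in this trial. The primary objective names reduction in costs together with health gain, although Table 2 lists cost-effectiveness among the secondary outcomes. Recruitment runs from primary care to university hospitals to obtain a mix of severity, so a wide baseline spread is plausible.

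**Working it through.** **The plan's own figure.** The article gives no figure for utilities, QALYs or costs. Its sample size is for the primary outcome: "With a presumed percentage of well-controlled preschool children with asthma-like symptoms of 20% in the usual care group" "and of 40% in the intervention group", for which "91 patients in both groups are needed to detect this difference with an alpha of 0.05 and a power of 80" per cent, with "Two-sided *p*-values < 0.05". Without continuity correction, n = [1.96·√(2·0.3·0.7) + 0.842·√(0.16 + 0.24)]² / 0.2² = 81.2, so 82. With the correction, n = (81.2/4)·[1 + √(1 + 4/(81.2·0.2))]² = 90.95, so 91. This matches exactly. Of 220 children, 10% dropout leaves 198, or 99 per arm, which is used below. Nothing that follows changes 91 or 220.

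**Assumptions, because the documents give none.** Utility SD 0.15 (range 0.10 to 0.25). Equal correlation ρ between any two visits, 0.3 to 0.7. QALY by the trapezium rule.

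**Weights with 3-monthly EQ-5D-Y.** There are nine visits over 2 years: 0.125 at each end and 0.25 at the seven between, 2.0 in total. The direct share of baseline is 0.125/2 = 6%. The sum of squared weights is 2·0.125² + 7·0.25² = 0.469.

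**Formulas.**
- Slope of QALY on baseline utility: b = 0.125 + ρ·1.875.
- Variance of QALY: V = SD²·[(1 − ρ)·0.469 + ρ·2²].
- SE of the QALY difference: √(2V/99).
- Share of variance removed by adjustment: R² = b²·SD²/V.
- SE of the baseline difference: 0.15·√(2/99) = 0.0213. The shift from a one-SE baseline difference is b·0.0213.

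**At ρ = 0.5.** b = 0.125 + 0.5·1.875 = 1.0625. V/SD² = 0.234 + 2 = 2.234. QALY SD = 0.15·√2.234 = 0.224. SE = 0.0319. R² = 1.129/2.234 = 0.51. Adjusted SE = 0.0319·√0.495 = 0.0224. Shift = 1.0625·0.0213 = 0.0227, which is 0.71 of the unadjusted SE.

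| ρ | Unadjusted SE | Adjusted SE | Variance cut | Shift for one-SE imbalance |
|---|---|---|---|---|
| 0.3 | 0.026 | 0.022 | 31% | 0.015 |
| 0.5 | 0.032 | 0.022 | 51% | 0.023 |
| 0.7 | 0.037 | 0.020 | 70% | 0.031 |

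Discounting the second year at 1.5% changes these little: at ρ = 0.5 the SEs are 0.0316 and 0.0222, and the shift is 0.0225. Over SD 0.10 to 0.25 and ρ 0.3 to 0.7 the shift runs from about 0.010 to 0.051.

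**In terms of power.** For a QALY difference of 0.4 SD, the unadjusted standardised effect is 0.4/√(2/99) = 2.81, giving 80% power. Dividing by √(1 − R²) gives 3.39 at ρ = 0.3 (92%) and 4.00 at ρ = 0.5 (98%).

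**Where the shift comes from.** At ρ = 0.5 only 0.125 of the slope of 1.0625 (12%) is the baseline's own weight. The rest is correlation with later values. At ρ = 0 a one-SE imbalance moves the QALY difference by only 0.002 to 0.004 over the SD range.

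**If EQ-5D-Y is annual.** The weights are 0.5, 1 and 0.5, so baseline carries 0.5/2 = 25%. With discounting, at SD 0.15 and ρ = 0.5, the SE falls from 0.035 to 0.023 (variance cut 57%) and the shift is about 0.027.

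**Costs.** The proportional variance reduction equals the squared correlation between baseline and follow-up costs. The documents give no figure, so no size is claimed.

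**The case against.** The strongest reply is that this is a condensed article. The full protocol, the analysis plan and any health-economic plan are not shown, and a regression equation for QALYs and costs often sits there. Bootstrap is also compatible with adjusted differences. So a reader might infer that the plan has decided against adjustment, but the text does not say that; it names no baseline term. The point survives in that form because the article does name methods: it refers to Table 2 for all of them, the tests there for EQ-5D-Y and costs are unadjusted, and the covariates it lists leave out both baseline values.

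A second reply is that nothing is invalid. This stands. Randomisation keeps the unadjusted difference unbiased over repeated trials, and the bootstrap carries chance imbalance as sampling error. The loss is in precision, and in accuracy given the imbalance that actually occurs.

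Two further inferences should be resisted. A reader might conclude that baseline imbalance could reverse the cost-effectiveness answer. The documents give no utility SD, expected QALY gain, cost difference or threshold, so this cannot be shown. By the same assumptions a 0.4 SD effect is 0.4·0.224 = 0.090 QALY, about four times the 0.023 shift. A reader might also suppose that pre-randomisation costs are counted in the totals. The article does not say so; they are simply an available covariate.

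**Conclusion.** The point holds as an inexpensive improvement to the stated method, not as an error that invalidates the analysis. No listed method for EQ-5D-Y, costs or cost-effectiveness uses the baseline values that are collected. Under the assumptions above (SD 0.15, 99 per arm, 3-monthly EQ-5D-Y), adjustment removes about half the variance of the QALY difference at correlation 0.5, with 31% and 70% at correlations 0.3 and 0.7. The shift from an ordinary chance imbalance is modest but not negligible against the standard error. It works mostly through correlation between visits and only slightly through the baseline's own 6% weight. All these sizes rest on an SD and a correlation that the documents do not give.

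The disagreement over the EQ-5D-Y schedule is a contradiction within the text and does not depend on any assumption. It matters here because it decides whether the direct baseline weight is about 6% or about 25%.

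**What to change.** In the section on health gain and costs of care, and in the cost-effectiveness row of Table 2, state that:

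- incremental QALYs are estimated by regression on arm, measurement centre and baseline EQ-5D-Y utility;
- incremental costs are estimated by regression on arm, measurement centre and costs in the 3 months before randomisation;
- both equations are bootstrapped together within arm (seemingly unrelated regression is one option), and the ratios and acceptability curves use the adjusted differences in costs and QALYs;
- the unadjusted ratio is reported as a sensitivity analysis.

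If a health-economic plan already says this, a reference to it is enough.

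Separately, make Participant timeline, Questionnaires and the health gain and costs section agree on how often EQ-5D-Y is completed.

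The cost is a few sentences and a few lines of code. Sample size and trial conduct do not change, and the baseline data are already planned. The one small drawback is that children with a missing baseline value need it imputed.
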